### **2.1.3 Outcome measures**

- Primary:

Olerud and Molander Ankle Score (OMAS): Is a self-administered questionnaire. It is a suitable outcome tool for assessing symptoms after an ankle fracture. The score is based on nine different items: pain, stiffness, swelling, stair climbing, running, jumping, squatting, supports and work/activities of daily living [10]. The scoring system correlates well with parameters considered to summarise the results after this type of injury.

- Secondary:

EQ-5D-5L: Is a validated, generic health-related quality of life measure consisting of five dimensions each with a 5-level answer possibility. Each combination of answers can be converted into a health utility score. It has good test-retest reliability, is simple for participants to use, and gives a single preference-based index value for health status that can be used for broader cost-effectiveness comparative purposes [11].

MOXFQ: Is a validated questionnaire which is self-reported (filled in by the participant). It contains 16 items, each with 5 response options comprising 3 separate underlying dimensions: Walking/standing problems (7 items), foot pain (5 items) and issues related to social interaction (4 items). Item responses are each scored from 0 to 4, with 4 representing the most severe state. The scale scores representing each dimension are produced by summing the responses to each item within that dimension. Raw scale scores are then converted to a metric (0-100; 100=most severe).

DRI: Is a self-administered questionnaire. It consists of 12 items specifically related to function of the lower limb. The DRI has been proven to be a practical clinical and research instrument, with good responsiveness and acceptability for assessment of disability caused by impairment in the lower limb [12].

Complications: All complications will be recorded, including mal-union, delayed/non-union, infection, wound complications, vascular injury, neurological injury, and venous thromboembolism. A record will also be kept of any other surgery required in relation to the index fracture. All baseline X-Ray/radiographs and also the last X-Ray/radiograph taken before the primary outcome point of 16 weeks will be collected.

Resource use questionnaires: The primary analysis will concentrate on direct intervention and healthcare/personal social services costs, while wider impact (societal) costs will be included within the sensitivity analyses. Relevant resource use questionnaires will be administered to participants at baseline and all follow-up points, to collect resource use data associated with the interventions under examination.

#### **2.1.4 Efficacy**

Primary: OMAS

Secondary: DRI, MOXFQ

All outcome measures will be paper based and collected at baseline (pre randomisation) face to face in the clinical setting. Subsequent data will be collected by postal questionnaire sent from Warwick CTU (WCTU) at six weeks, 10 weeks, 16 weeks, 24 weeks and 24 months post randomisation. MOXFQ will be collected at 16 weeks only.

#### **2.1.5 Safety**

Adverse event data

At each data point participants will be asked by postal questionnaire sent from WCTU if they have had any adverse events and how they were managed. Additionally, PIs will be asked to comply with procedures for reporting Serious Adverse Events (SAEs) to the AIR central office within 24 hours of becoming aware of an event.

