Four hundred and seventy eight participants will be randomised in total, across participating centres. Both interventions are currently used in the NHS, consequently delivery of the randomised allocation will follow normal practice. The participants will then attend follow up appointments as per routine clinical practice. All trial related follow up will be completed through postal follow up centrally from Warwick CTU at six weeks, 10 weeks, 16 weeks, 24 weeks, 12 months, 18 months and 24 months post randomisation. At each follow up (except 12 and 18 months) complications, functional status (OMAS and DRI), health related quality of life (EQ-5D-5L) and resource use questionnaires will be collected. For the 12 and 18 month data point only EQ-5D-5L and resource use will be collected. Sixteen weeks will be the primary end point and also include functional status measured by MOXFQ.

The local principal investigator and research team at each site cannot be blind to treatment as they will be delivering the interventions. None of these team members will have a role in the collection of follow up participant data beyond reporting serious adverse events.

A trial management group (TMG), trial steering committee (TSC) and data monitoring and ethics committee (DMC) will oversee the trial.

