### **2.1.2 Secondary objective**

Secondary Objectives:

- 1) To quantify and draw inferences on observed differences in ankle function assessed using the OMAS score at 6 weeks, 10 weeks, 24 weeks and 24 months and MOXFQ 16 weeks after randomisation.
- 2) To quantify and draw inferences on observed differences in health related quality of life (EQ5D-5L) between trial treatment groups at 6 weeks, 10 weeks, 16 weeks, 24 weeks, 12 months, 18 months and 24 months after randomisation.
- 2) To quantify and draw inferences on observed differences in disability rating (DRI) between trial treatment groups at 6 weeks, 10 weeks, 16 weeks, 24 weeks and 24 months after randomisation.
- 3) To quantify and draw inferences on observed differences on complication rates between trial treatment groups at 6 weeks, 10 weeks, 16 weeks, 24 weeks and 24 months after randomisation.
- 4) To estimate comparative cost-utility of the two trial treatment groups and collect resource use data at 6 weeks, 10 weeks, 16 weeks, 24 weeks, 12 months, 18 months and 24 months after randomisation.

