## **2.10 End of trial**

The trial will end when all participants have completed their 24 month follow-up.

The trial will be stopped prematurely if:

- Mandated by the Ethics Committee
- Following recommendations from the Data Monitoring Committee (DMC)
- Funding for the trial ceases

The Research Ethics Committee will be notified in writing within 90 days when the trial has been concluded or within 15 days if terminated early.

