| Complications                              |                  |          | ✓                               | ✓                                | ✓                                  | ✓                                  |                                 |                                 | ✓                               |

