#### **6.2.3.3 Secondary outcome analysis**

Descriptive statistics of patient reported outcome measure (PROM) data (i.e. OMAS, MOXFQ, EQ5D and DRI) at each time point will be constructed with between group analyses following the method set out for the primary analysis above. Patterns of recovery will also be explored.

Complications will be summarised with between groups comparisons evaluated using chi-squared tests. Temporal patterns of any complications will be presented graphically and if appropriate, a time-to-event analysis (e.g. Kaplan-Meier survival analysis) will be used to assess the overall risk and risk within individual classes of important complications (e.g. non-union).

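### Section 2.1.5 asks participants about adverse events at every data point, but section 2.1 and Table 1 omit this at 12 and 18 months, leaving participant-reported events after week 24 to one long recall

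*Protocol*

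**What the plan says.** On who is asked and when, Protocol section 2.1.5 (Safety) states: "At each data point participants will be asked by postal questionnaire sent from WCTU if they have had any adverse events". The next sentence adds a separate route, in which principal investigators report serious adverse events (SAEs) within 24 hours of learning of them.

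Section 2.1 places the central postal follow-ups "at six weeks, 10 weeks, 16 weeks, 24 weeks, 12 months, 18 months and 24 months post randomisation". It then sets the content: "At each follow up (except 12 and 18 months) complications, functional status (OMAS and DRI") and the other questionnaires. For the two later points it says: "For the 12 and 18 month data point only EQ-5D-5L and resource use will be collected".

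Table 1 (section 3.1) has a row headed "Complications". It is ticked at 6, 10, 16 and 24 weeks and at 24 months, and is blank at 12 and 18 months. The table has no separate adverse-event row. The objective in section 2.1.2 follows the same five times: "observed differences on complication rates between trial treatment groups at 6 weeks, 10 weeks, 16 weeks, 24 weeks and 24 months after randomisation". The trial summary does likewise.

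Section 2.1.3 undertakes to record all complications, naming mal-union, delayed or non-union and further surgery on the index fracture among them. Section 6.2.3.3 compares complications between groups with chi-squared tests and plots their timing. Where judged appropriate, "a time-to-event analysis (e.g. Kaplan-Meier survival analysis) will be used to assess the overall risk". On duration, section 2.10 says: "The trial will end when all participants have completed their 24 month follow-up".

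**The concern.** The case report forms cannot satisfy both statements. Section 2.1.5 requires an adverse-event question at all seven follow-ups, while section 2.1 excludes it from two of them.

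If the narrower schedule is used, participants are not asked about complications between 24 weeks and 24 months. Problems with union and further surgery on the fracture can come to light in that period. Three consequences follow for participant-reported events:

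- They are remembered over a long interval, so some may be forgotten or misdated.
- They are lost if the participant does not respond at 24 months, even if the participant replied at 12 and 18 months.
- Participants know their allocation (section 2.8.1), so recall could differ by arm.

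Complications are a stated secondary outcome. Section 1.2 also says the possible benefits of bracing have to be weighed against more adverse events, so harms data carry real weight in this comparison.

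**Working it through.** The protocol gives no figure for the length of this gap, so there is none to reproduce. The check has two parts.

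**1. Are the statements compatible?**

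- Section 2.1.5: adverse events asked by post at every data point.
- Section 2.1: 12 and 18 months are each called a data point, and their content is limited to two instruments, neither of which is an adverse-event question.
- Table 1, section 2.1.2 and the trial summary: complications at five times, excluding 12 and 18 months.

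One might argue that adverse events and complications are different items, so that Table 1 does not speak to section 2.1.5. The restriction in section 2.1 settles this: it excludes anything beyond EQ-5D-5L and resource use, whatever the item is called.

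**2. How long is the gap?**

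Inputs: last early questionnaire at 24 weeks and next complications questionnaire at 24 months (section 2.1, Table 1); visit windows of ±4 weeks and ±1 month (Table 1). Weeks per month = 365.25 / (12 × 7) = 4.348.

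- Share of follow-up, with 24 months as 104 weeks: (104 − 24) / 104 = 80 / 104 = 76.9%. With 24 months as 2 × 365.25 / 7 = 104.36 weeks: 80.36 / 104.36 = 77.0%.
- Length: 80 / 4.348 = 18.4 months, or 80.36 / 4.348 = 18.5 months.
- Shortest within the windows: 23 months − 28 / 4.348 = 23 − 6.4 = 16.6 months.
- Longest within the windows: 25 months − 20 / 4.348 = 25 − 4.6 = 20.4 months.
- If section 2.1.5 were followed, at nominal times: 12 − 24 / 4.348 = 12 − 5.5 = 6.5 months to the 12-month form, then 6 and 6 months. The longest gap is about 6.5 months.

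**3. What else covers that interval?**

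- SAEs: section 4.2 has them reported from consent to two years, with start and end dates. Section 4.1.3 lists the expected ones, including wound complications, infection, thromboembolism and secondary operations for malunion, non-union or metalwork.
- Limits of that route: reporting starts when the investigator learns of the event (sections 2.1.5, 4.2), and section 4.3 has the investigator check when participants attend. Trial follow-up is postal, and Table 1 lists no site assessment after baseline.
- Non-serious events: section 4.2 asks investigators to report these too. However, section 2.1 gives site teams no part in follow-up data beyond SAEs. Section 5.1 has sites complete forms at baseline and for SAEs, with everything else coming from participants by post. These events therefore depend mainly on the questionnaire.

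**The case against.** The strongest reply is that the schedule is consistent and section 2.1.5 is one loose phrase. Section 2.1, Table 1, section 2.1.2 and the trial summary agree on five times. Section 2.1.4, just before the safety text, lists those same five for the efficacy measures, and section 2.1.6 reserves all seven for health economics. Short mailings at 12 and 18 months are a deliberate choice, and naming the time points in section 2.1.5 would remove the conflict. This is a fair account of how the conflict may have arisen, and it is the minimum correction. It would leave the 18.5-month gap in place.

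A reader might also infer more than the documents support:

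- *That all harms in the last 77% of follow-up rest on one recall.* They do not. Sites report SAEs throughout, and the expected SAEs overlap heavily with the late complications of most interest.
- *That someone missing the 24-month form contributes no complication data after week 24.* This holds only for participant-reported data. SAE reports may still exist. Section 2.6.2 allows telephone completion, and allows hospital records to be used for those who stop questionnaires. Resource-use forms at 12 and 18 months and routine data (section 6.6) may show treated problems, although the protocol does not name them as sources for the complications outcome and the forms are not shown.
- *That a planned survival analysis is undermined.* Section 6.2.3.3 makes that analysis conditional, so the point applies only if it is done.
- *That 77% of late events would be missed.* The figure is a share of calendar time. The protocol gives no late-event rate, so the number under-reported cannot be estimated.

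**Conclusion.** The contradiction is certain and the passages must be reconciled. If section 2.1 and Table 1 govern, participant-reported events, mainly non-serious, have a single collection point for about 80 of 104 weeks (77%). Recall is about 18.5 months, or 16.6 to 20.4 months across the visit windows. Non-response at 24 months removes participant-reported complication data after week 24. SAE reporting to two years reduces the loss, but it relies on site awareness.

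The arithmetic assumes only the nominal times and windows in Table 1. That recall would be incomplete, misdated or different by arm is plausible, but the protocol has no data on it. The 16-week primary endpoint is unaffected. This is worth correcting because a stated secondary outcome is involved and the remedy is cheap.

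**What to change.** Reconcile in favour of section 2.1.5:

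- Add the existing complications/adverse-event page, with event dates, to the 12- and 18-month questionnaires.
- Tick Complications at visits 7 and 8 in Table 1.
- Amend the content statement in section 2.1, and the complication objectives in section 2.1.2 and the trial summary, to match.

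The cost is slightly longer forms at two mailings that already go out, some extra data entry and a protocol amendment. No visit or mailing is added and treatment is unchanged.

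If the sponsor prefers to keep the short mailings, section 2.1.5 should name its five time points. The report should then state that participant-reported complications between 24 weeks and 24 months come from one questionnaire.

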#### **2.1.6 Others**

Health economics

All outcome measures will be paper based and collected at six weeks, 10 weeks, 16 weeks, 24 weeks, 12 months, 18 months and 24 months post randomisation by postal questionnaire sent from WCTU.

### **2.2 Eligibility criteria**

Eligible to be included in the trial if potential participants meet the following criteria:

#### **2.2.1 Inclusion criteria**

1. Provision of written informed consent
2. Aged 18 years or over

3. A closed ankle fracture for which the treating clinician would consider plaster cast a reasonable management option.
4. Within 3 weeks of operative management or injury if non-operative.

### **2.2.2 Exclusion criteria**

1. Ankle fracture secondary to known metastatic disease.
2. Complex intra-articular fracture (e.g. Pilon fracture)
3. In the opinion of the surgeon the patient would require manipulation and close contact casting.
4. In the opinion of the surgeon the patient would require manipulation and moulded cast.
5. Wound complication that would contraindicate fixed angle removable orthotic intervention.
6. Previous ankle fracture randomised in the present trial.
7. Evidence that the patient would be unable to adhere to trial procedures or complete postal questionnaires.
8. Known pre-existing neuropathic joint disease contraindicating FARO intervention

## **2.3 Participant identification / Screening**

New patients with an ankle fracture are reviewed each day by the trauma team either as inpatient admissions on the trauma ward or as an outpatient in fracture clinic. Following identification of a potential participant with a new ankle fracture by the trauma team a suitably trained member of the research team at each site will be contacted to undertake paper eligibility checks in conjunction with the trauma team. The research team member will complete the eligibility checklist and sign to confirm that eligibility checks were made in conjunction with and have been verified by a suitably qualified member of the trauma team. The trauma team member will then document this on the patient file, a quality assurance plan to check this process will be detailed further in the monitoring plan held at WCTU.

All people meeting the entry criteria will be checked for eligibility and entered on the monthly screening log. All eligible potential participants who are willing to be approached by a suitably trained member of the research team will be provided with verbal and written information about the study. If potential participants do not undergo surgery they will be then be asked if they wish to take part in the study. All new non-operatively managed potential participants will have a maximum of 21 days from injury to make a final decision.

If potential participants do undergo surgery, the suitably trained member of the research team will re-approach the participant for consent when they return for a wound check (usually 14 days, up to maximum of 21 days), at an outpatient appointment.

To ensure all members of the trauma team are informed of the study, and to raise the profile of the study, where possible, publicity posters will be placed in clinical areas.

## **2.4 Site Staff Training**

An appropriately trained member of the research team will be responsible for confirming eligibility with trauma teams, obtaining consent, collecting baseline data and subsequent SAE reporting. The

Trial Manager will provide training to complete these tasks via a presentation outlining an overview of the trial (key personnel, protocol, management and oversight) and clinical reporting form (CRF) completion, such as SAE reporting, withdrawals, screening logs and data clarifications. This training will take place prior to recruitment with the local PI and research team who will carry out trial related procedures.

This local team will then be responsible for distribution of the training materials across the wider trauma team using opportunities to present during clinical training and departmental meetings on an ad hoc basis. This wider training will occur throughout the recruitment phase due to the nature of rotating and changing trauma staff members.

When a new research team member or PI is appointed at local sites the Trial Manager will be responsible for re-distributing trial-training materials and ensuring delegation logs are updated.

No specific training on administering trial interventions is required as they are used as part of routine clinical practice for a range of trauma and orthopaedic presentations.

## **2.5 Informed consent**

Consent materials:

Potential participants will be provided with verbal and written information about the study. A list of information the research team should cover before consent is obtained will be provided to ensure that all essential information is discussed with the potential participant.

Timing of consent:

Written informed consent will be obtained by a suitably trained member of the research team at each site as per the delegation log, after allowing sufficient time for the potential participant to consider their decision and ask questions about the trial. Sufficient time for some potential participants may result in a decision to take part in the trial immediately after receiving all relevant information; this is reflective of clinical practice. Alternatively, if potential participants would like to leave the clinic with the information and make a decision at a later date of their choosing, they will be free to do so within the time limits specified in the section entitled 'intervention'. The definition of 'sufficient time' is at the discretion of the potential participant being approached to take part.

Consent responsibility:

The PI retains overall responsibility for informed consent at their site and will ensure that any person delegated responsibility to participate in the informed consent process is duly authorised, trained, qualified and competent.

New information:

Any new information that arises during the trial that may affect participants' willingness to take part will be reviewed by the TSC; if necessary this will be communicated to all participants. A revised consent form will be completed if necessary.

Participants GP will be informed by letter that they are taking part in this clinical trial. Participants may decline their GP being informed of their participation in the trial involvement by not initialling the appropriate box on the consent form.

Decline/withdrawal:

The right of a potential participant to refuse participation without giving reasons will be respected, and recorded on the screening log. The participant will remain free to withdraw at any time without giving reasons and without prejudice to any further treatment, and will be provided with a contact point where he/she may obtain further information about the trial.

## **2.6 Randomisation**

### **2.6.1 Randomisation**

Pre-randomisation eligibility checks will be carried out to ensure that potential participants meet the eligibility criteria and are not randomised in error. Written informed consent for entry into the trial and baseline assessment must be obtained prior to randomisation. Subjects will be randomised strictly sequentially, as they become registered as eligible for randomisation on the web based system. Allocation concealment will be maintained by an independent randomisation team who will be responsible for generation of the sequence and will have no role in the allocation of participants.

The treatment group will be allocated by computer using a minimisation algorithm with a random element and stratification by centre, age and operative/non operative management following use of a secure web based randomisation service. Minimisation is a better option than conventional stratification with variable block sizes, due to the relatively small number of participants expected in some strata. The randomisation service will be available 24 hours a day, seven days a week to facilitate the inclusion of all eligible participants. The randomisation system will allocate each participant a unique trial number. A confirmation email will be automatically generated to the research site containing the randomisation details. A member of the research team will inform the relevant trauma team member who routinely administers the trial interventions. The trauma team member will then administer the treatment allocation.

Stratification by centre will help ensure that any clustering effect related to the centre itself will be equally distributed in the trial arms. Stratification on the basis of age will be used to ensure that younger participants with normal bone quality sustaining high-energy fractures and older participants with low-energy (fragility) fractures related to osteoporosis are also balanced between arms. The age group stratification will also be used as a proxy for bone density.

In a large study in Norway involving 7600 participants, found that bone mineral density remains stable up until the age of 50 years. After the age of 50, bone mineral density decreased steadily in males, whilst in females there was an initial decline between the ages of 50 and 65, with a further decline in the age groups thereafter [13]. A recent study by Court-Brown [1], assessed over 1000 patients with a fracture. This study confirmed that there is a clear bimodal distribution according to the age of the patient. The crossover of the two peaks of incidence was around 50 years of age. These studies provide strong evidence that patients over the age of 50 become increasingly vulnerable to fragility fractures. Based on this information; and to align with recently published NIHR multi centre RCTs on ankle fracture management [14], we have chosen an age of 50 as the stratification cut-off for this trial.

A final stratification based on operative/non operative presentation will be implemented. This will be used to estimate the extent of the ligamentous injury and the stability of the joint. It will ensure that any effect related to severity of injury is equally distributed amongst the trial arms.

